## Abstract

**Background:**

Total hip replacement has recently followed a progressive evolution towards principles of bone- and soft-tissue-sparing surgery. Regarding femoral implants, different stem designs have been developed as an alternative to conventional stems, and there is a renewed interest towards short versions of uncemented femoral implants. Based on both experimental testing and finite element modeling, the proposed study has been designed to compare the biomechanical properties and clinical performance of the newly introduced short-stem Minima S, for which clinical data are lacking with an older generation stem, the Trilock Bone Preservation Stem with an established performance record in short to midterm follow-up.

**Methods/design:**

In the experimental study, the transmission of forces as measured by cortical surface-strain distribution in the proximal femur will be evaluated using digital image correlation (DIC), first on the non-implanted femur and then on the implanted stems. Finite element parametric models of the bone, the stem and their interface will be also developed. Finite element predictions of surface strains in implanted composite femurs, after being validated against biomechanical testing measurements, will be used to assist the comparison of the stems by deriving important data on the developed stress and strain fields, which cannot be measured through biomechanical testing. Finally, a prospective randomized comparative clinical study between these two stems will be also conducted to determine (1) their clinical performance up to 2 years’ follow-up using clinical scores and gait analysis (2) stem fixation and remodeling using a detailed radiographic analysis and (3) incidence and types of complications.

**Discussion:**

Our study would be the first that compares not only the clinical and radiological outcome but also the biomechanical properties of two differently designed femoral implants that are theoretically classified in the same main category of cervico-metaphyseal-diaphyseal short stems. We can hypothesize that even these subtle variations in geometric design between these two stems may create different loading characteristics and thus dissimilar biomechanical behaviors, which in turn could have an influence to their clinical performance.

**Trial registration:**

International Standard Randomized Controlled Trial Number, ID: ISRCTN10096716. Retrospectively registered on May 8 2018.

**Electronic supplementary material:**

The online version of this article (10.1186/s13063-019-3445-x) contains supplementary material, which is available to authorized users.

## Background

Total hip arthroplasty (THA) for the treatment of advanced hip osteoarthritis is considered one of the most successful surgical procedures of the last century, aiming to relieve pain and improve function of the hip joint [1–5]. Conventional, cementless long stems have shown 10-year survival rates of more than 90% [6–8] but as THA is increasingly performed in younger and more active patients [9], recent implant developments are aimed towards minimizing tissue damage and preserving bone stock without compromising implant stability [10]. As the novel concept of patient fast-tracking with less invasive interventions concerns not only the surgical approaches or the blood loss but the materials as well, many manufacturers have designed short-stem implants using different proximal geometries and design philosophies. Short stems have been designed in a way to better fit in the metaphysis of the proximal femur thus reproducing a biomechanical behavior more similar to the physiological bone. The clinical impact of these innovations would be a more accelerated rehabilitation program, improved long-lasting functional outcome and mainly, preservation of bone stock for future revisions. A rigid primary fixation and a larger area of metaphyseal contact are the essential requirements for a successful osteointegration of these shorter stems with an ultimate goal to produce a more physiological load transfer to the femur thus eliminating the stress-shielding effect of the standard long stems. However, these hypothetical benefits still need to be verified [11].

The idea of short-stem hip arthroplasty was first reported by Judet and Judet in 1940 [12] with less satisfactory outcomes [13, 14]. The next model, the Mayo Conservative Hip (Zimmer, Warsaw, IN, USA) was designed to anchor in a larger fixation area [15] and has been in clinical practice for more than 20 years since. In 2000, Morrey et al. [16] reported a 94% survival rate after a mean follow-up period of 6.2 years. Since then, a wide variety of new models of short stems have emerged, with differences in operative technique and method of fixation [17, 18]. Due to a lack of adequate regulation, many innovative hip implants were easily adopted by clinicians without sound premarketing testing and high-quality evidence supporting their clinical use.

From the biomechanical perspective, initial stability and initial lack of motion at the bone-prosthesis interface are essential for long-term survival rates and, therefore, accuracy of host bone preparation and prosthesis design are crucial, whereas implant surface texture and quality of the bone-implant contact determine secondary stabilization of the prosthesis. Various techniques of measuring the cortical deformation pattern as a result of implantation with different prostheses have been described in the literature. Experimental testing employing strain gauges constitutes the most common technique for measuring strain fields in the assessment of post-implantation bone response in vitro [19–23]. However, a major limitation of this technique is that the information is provided from the attachment site only. Recently, digital image correlation (DIC), a non-contact optical metrology method, has gained popularity due to its capacity to extract full-field surface-strain measurements of objects subjected to external loads [24–27]. In addition, the Finite element analysis (FEA) method has been well established as another tool of calculating deformation, strain and stress patterns in implanted bones [28, 29]. Finite element (FE) models provide three-dimensional (3D) strain predictions in implant-bone constructs and enable analyses of the developed stress and strain fields in areas where strains cannot be experimentally measured, such as the bone-implant interface. However, the assumption of simplified bone material properties, geometry and loading conditions is often made in most of parametric 3D FE models and thus their validation using experimental tests is recommended wherever it is possible [24, 30, 31].

The proposed study has been designed to compare the biomechanical properties, based on both biomechanical tests and FE models, as well as the clinical performance of two different metaphyseal-fitting short stems; the TRI-LOCK Bone Preservation Stem (DePuy Orthopaedics Inc. Warsaw, IN, USA) and the Minima S Femoral Stem (Lima corporate Villanova di San Daniele, Italy) (Fig. 1).

**Fig. 1 Fig1:**
[figure not shown]
The two different stems that will be compared in the study **a**. Trilock Bone Preservation Stem, **b**. Minima S

In the experimental study, the transmission of forces as measured by cortical surface-strain distribution in the proximal femur will be evaluated using DIC, first on the non-implanted femur and then on the implanted TRI-LOCK Bone Preservation Stem (BPS) and Minima S femoral stems. The strain patterns of the non-implanted femur will served as the control group. The primary outcome would be to check the presence of adequate metaphyseal anchorage and the effect of the two different-design short stems on the strain patterns compared to the unimplanted femur.

Finite element parametric models of the bone, the stem and their interface will be also developed. Finite element predictions of surface strains in intact and implanted composite femurs, after being validated against biomechanical testing measurements, will be used to assist the comparison of the stems by deriving important data on the developed stress and strain fields, which cannot be measured through biomechanical testing.

A prospective randomized comparative clinical study between these two types of short stems, will be also conducted to determine (1) their clinical performance up to 2 years’ follow-up using validated scoring instruments and gait analysis parameters; (2) stem fixation and bone remodeling using a detailed radiographic analysis and (3) incidence and types of complications if any.

## Methods/design

### Biomechanical study

The experimental work will be undertaken in the Laboratory of Technology and Strength of Materials at the Department of Mechanical Engineering and Aeronautics of Patras University.

#### Implant systems

Two implant systems will be used, the TRI-LOCK Bone Preservation Stem (DePuy Orthopaedics Inc. Warsaw, IN, USA) and the Minima S Femoral Stem (Lima corporate Villanova di San Daniele, Italy). The technical characteristics of these stems are summarized below:Tri-Lock BPS (DePuy, Johnson & Johnson, Warsaw, IN, USA) is a short, tapered-wedge, proximally porous-coated titanium femoral stem. Compared to its clinically successful predecessor, the Tri-Lock standard stem, the BPS stem is shorter, has a narrower distal segment, and features a curved distal tip. Also, the Tri-Lock BPS has a highly porous pure titanium (“GRIPTION®”) coating on the proximal 50% portion that is engineered to provide an increased surface roughness when compared to POROCOAT® porous coating, which is on the original TRI-LOCK stem. The TRI-LOCK BPS is available in 13 stem sizes (size 0–12/length 95–119 mm) with standard and high offset options for all stem sizes. The high offset option provides direct lateralization, thus increasing offset without affecting either the leg length or the neck-shaft angle, which remains constant at 130^0^Minima S Monolithic Femoral Stem (Lima corporate Villanova di San Daniele, Italy) is a short, curved, four-tapered, proximally porous-coated titanium femoral stem. It is comprised of 12 stem sizes (size 1–12/length 82–118 mm) in standard and lateralized configuration. The standard versions have a neck-shaft angle of 134°, while the lateralizing versions have a neck-shaft angle of 131°. The Minima S stem has a tapered and medially side-sharpened tip aiming to reduce the risk of contact with the cortical medial wall

#### Study aims

Although both stems belong to the same short-stem family, the Tri-Lock BPS is a stem with a geometrical design similar to conventional long stems (its design is based on its clinically successful predecessor, the Tri-Lock standard stem), but shorter with a narrower distal segment. On the other hand, the Minima S stem is even shorter, has an anatomic shape following the natural curvature of the medial calcar, preventing breach of the greater trochanter and a medially sidecut tip to reduce the risk of contact with the cortical medial wall.

We can hypothesize that the above variations, regarding stem length and geometric design, may create differences in strain distribution and thus dissimilar biomechanical behaviors. Specifically, we sought to determine if the implantation of a shorter, anatomically shaped stem would produce a pattern of strain distribution closest to normal, reduce the risk of distal locking and proximal offloading. Therefore, strain patterns after implantation of the Minima S stem are compared to both strain patterns without an implanted stem and strain patterns following implantation of the Trilock BPS stem.

#### Preparation of the femurs

Seven fourth generation, medium composite, femurs from Sawbones Europe (Malmö, Sweden) with identical design and material properties will be used in accordance to previous biomechanical studies [13, 32–37]. Three different composite femoral bones for each prosthesis will be prepared by the same investigator ([name]) according to the manufacture’s surgical technique. Also, a set of three tests will be repeated for each specimen. The quality of implantation in terms of correct implant size and positioning (anteversion) will be assessed using antero-posterior and lateral radiographs. After the radiographic evaluation, the implanted femurs will be fixed into a steel cylinder using a standardized embedding procedure based on a previously reported femur-aligned reference system [38]. During the embedding procedure, a custom alignment fixture will be used, ensuring that the central axis of the femur through fossa piriformis coincides with the central axis of the cylinder. The femurs will be fixed in neutral position on the sagittal plane, using the posterior condylar surface as reference for rotational alignment and at 11^0^ of adduction in frontal plane, to simulate the physiological inclination during single-leg stance [39]. The distal condyles of the intact femur will be embedded into the steel cylinder using the same embedding protocol as described above. The proximal end of each femur will then be prepared for DIC measurements. A layer of matt-white paint, followed by black speckles will be applied creating a high contrast, random speckle pattern.

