#### Statistical analysis

Statistical analysis will be performed using SPSS Statistics (Version 23, IBM SPSS, Armonk, NY, USA). Normal distribution of the parameters of interest, namely axial construct stiffness, failure load, and cycles to failure in each study group will be screened with Shapiro-Wilk test. Homogeneity of variances between the groups will be checked with the Levene test. Significant differences between the two groups will be checked with paired-samples *t* test. A *P* = .05 level of significance will be set for all statistical tests.

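### One intact femur serves as the control for the bench study's primary comparison, and the planned paired t test does not fit a design with different bones per stem

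*Protocol article*

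**What the plan says.** All references are to the Protocol article.

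- **Specimens (Preparation of the femurs).** The total is "Seven fourth generation, medium composite, femurs". On allocation: "Three different composite femoral bones for each prosthesis will be prepared by the same investigator". On repetition: "a set of three tests will be repeated for each specimen".
- **Order of work (same section).** "After the radiographic evaluation, the implanted femurs will be fixed into a steel cylinder". The unimplanted specimen is handled separately and in the singular: "The distal condyles of the intact femur will be embedded into the steel cylinder". Speckling for image correlation comes after embedding. No intact test of the six bones that receive a stem is described.
- **Role of the intact femur (Background, after Fig. 1).** "The strain patterns of the non-implanted femur will served as the control group". The primary bench outcome stated there covers metaphyseal anchorage and each stem's effect on strain relative to unimplanted bone.
- **Comparisons (Biomechanical study, Study aims).** "strain patterns after implantation of the Minima S stem are compared to both strain patterns without an implanted stem", and also to those with the other stem.
- **Test (Biomechanical study, Statistical analysis).** "Significant differences between the two groups will be checked with paired-samples" *t* test, at the .05 level. The variables listed are stiffness, failure load and cycles to failure. Strain is not among them, and no separate test of intact against implanted bone is named.

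**The concern.** Two stems with three bones each use six of the seven femurs, so the control is a single specimen. Its three tests are repeat readings of one bone in one embedding. They show how repeatable the loading and imaging are, but not how much intact specimens differ from one another. Any peculiarity of that specimen or its mounting enters every contrast with unimplanted bone, for both stems alike.

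The named test adds to the difficulty. A paired test needs matched values, and no bone carries both stems or is described as tested both intact and implanted. The only values available for matching are repeat readings or load steps, and these are not independent replicates. At stake is what the bench study can validly conclude on its own primary outcome. The randomised clinical comparison is not affected.

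**Working it through.** **1. Specimen count.** 2 stems × 3 bones = 6, and 7 − 6 = 1 intact femur. The stated total is reproduced as 3 + 3 + 1. The article gives no power calculation for the bench study, so there is none to reproduce.

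**2. What one control allows, with the bone as the unit.** Average the three tests within each bone and let SD be the between-bone standard deviation of these means. The intact group has 1 − 1 = 0 df of its own. If the implanted bones are assumed to have the same variance, the standard error of implanted minus intact is √(1/3 + 1/1) = 1.155 SD. Detectable differences at two-sided 5% (sidedness is assumed) and 80% power, from the noncentral t distribution:

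| Comparison | SE (SD) | df | Critical t | Detectable difference (SD) |
|---|---|---|---|---|
| 1 v 3, variance from one stem | 1.155 | 2 | 4.303 | 6.53 |
| 1 v 3, variance pooled over both stems | 1.155 | 4 | 2.776 | 4.34 |
| 3 v 3, for reference | 0.816 | 4 | 2.776 | 3.07 |

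In simulation, the 1 v 3 test on bone means kept a type I error of about 5% at every variance share tried. The test is valid under its assumption, but very weak.

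**3. If readings were treated as independent.** Simulation with no true difference, three readings per bone and 40,000 runs per setting. The share of variance that lies between bones is an assumption, because the article gives no value.

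| Between-bone share | Intact v one stem, 3 v 9 readings | Stem v stem, 9 v 9 readings |
|---|---|---|
| 0 | 5% | 5% |
| 0.2 | 10% | 10% |
| 0.5 | 20% | 18.5% |
| 0.8 | 32% | 28% |

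**4. The paired test between stems.** Pairing three bones of one stem with three unrelated bones of the other leaves 2 df instead of 4. Three pairs have 80% power for 3.26 SD of the differences. For unrelated bones the SD of a difference is √2 SD, so this is 3.26 × 1.414 = 4.61 SD, against 3.07 SD for the unpaired test. The result would also depend on which bones happened to be paired.

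**5. Each bone as its own control.** With within-bone correlation r, and ignoring reading error, the standard error of the mean implanted-minus-intact difference over three bones is √(2(1 − r)/3) SD:

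- r = 0: 0.82 SD
- r = 0.5: 0.58 SD
- r = 0.8: 0.37 SD
- r = 0.9: 0.26 SD

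The value with one control is 1.155 SD. The gain at r = 0 comes only from having three intact set-ups instead of one. The rest depends on r, which is unknown.

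**The case against.** **Composite bones vary little.** The Limitations section on the biomechanical study chooses them for that reason, and the femurs are described as identical in design and material. This is a fair rationale for few specimens, and it means that the between-bone share could lie at the low end of the table. It does not cover the steps done afresh for each specimen: embedding and alignment, the glued abductor rod and the speckle pattern. Three tests on one set-up do not sample these, and no SD is given.

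**The control may not be a single bone.** The Background describes measuring the non-implanted femur first and the implanted stems afterwards, and the finite element section speaks of intact bones in the plural. If every bone were tested before and after, there would be three pairs per stem. The preparation section describes a different sequence, and a seventh femur would then not be needed. One control remains the clear reading, although the article never states the number.

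**The stem contrast does not need the control.** With a shared reference I, (M − I) − (T − I) = M − T, so the signed difference between stems rests on 3 v 3 bones. That stands. Each stem's distance from intact bone, which is what the primary outcome concerns, still depends on I.

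**Stronger readings.** A reader might infer that the intact comparison has no error term and cannot be tested at all. Step 2 shows that it can, under an assumption. A reader might also infer that repeat readings will be counted as replicates. The article does not say so. It leaves the unit of analysis open, names no intact-versus-implanted test, and is compatible with a descriptive comparison of strain maps. A condensed article may leave the unit to a fuller plan, but the specimen count and the paired test are stated here and do not fit together.

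**Conclusion.** The point holds as a weakness of the bench component. A single intact femur gives the control condition no between-specimen variance, and an error in its set-up moves the reference for both stems. A formal comparison is possible only with variance borrowed from the implanted bones. It would then have 80% power only for differences of about 6.5 SD (2 df) or 4.3 SD (4 df). The equal-variance assumption cannot be checked with one control, and it is doubtful because implantation may add variation of its own.

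The paired-samples test is wrong for a comparison of stems placed in different bones. The false-positive rates of 10% to 32% are conditional: they apply only if readings are analysed as independent, and only at the assumed variance shares. At a share of zero the rate is the nominal 5%. They measure a risk that the article leaves open and do not describe a stated plan.

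**What to change.** 1. Average the three tests per femur and state that the femur is the unit of analysis. This costs only wording.
2. Replace the paired test between stems with an unpaired comparison of three bones against three. This also costs only wording.
3. Where feasible, load each of the six femurs intact under the same image-correlation procedure before its stem goes in. Repeat after implantation and analyse implanted minus intact per femur. This needs no extra femurs, but about 6 × 3 = 18 more loading runs, a changed embedding order and renewed speckling. Remounting adds an error that step 5 of the working leaves out. The precision gain depends on the within-bone correlation and may be small if the bones are near-identical.
4. If intact-first testing is not feasible, state that one intact femur is used and report the comparison with it descriptively, without P values.

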#### The loading jig

For the purpose of the experimental study, a custom-made mechanical jig has already been designed and manufactured according to the standardized protocol for testing conditions during functional validation of hip prostheses, as reported by Cristofolini and Viceconti [39]. In order to be able to apply the required forces at the desired direction and having the correct magnitude a modular fixture device had to have the following basic characteristics:The basic fixture components used for the application of forces on the bone had to be adjustableTwo load cells had to be used, so that the two forces, on the femoral head and the greater trochanter, could be measuredGoniometers and rulers are used to verify the correct geometrical features of the fixture

The design of the developed fixture is presented in Fig. 2a. It comprises two parts; one positioned on the top of the bone to apply forces on the femoral head and the greater trochanter and one used for constraining the femur distally. The top part consists of a metal beam with an acetabular component attached to its undersurface, creating an articulation with the femoral head. The acetabular cup had an inclination of 45^o^ and 0^o^ anteversion. The beam is supported laterally on the femoral head through the acetabular cup and is attached medially to the load cell of a computer-controlled electromechanical testing machine. A system of rulers and goniometers allowed the position and direction of the forces to be accurately controlled.

